### 2.1. Design

This is a two-arm parallel-group feasibility RCT, in which families will be randomly assigned to an intervention arm and a waitlist control arm, with a 1:1 allocation ratio. Parents in the intervention group will participate in the Being a Parent program, while the waitlist control group will not receive any intervention during this phase but will be given the opportunity to participate in the program after post-intervention assessments are conducted. Two outcome assessments will be completed by both arms at baseline and post-intervention, and an additional 6-month follow-up will be conducted only with the intervention arm, as assessing the control group at this stage would not provide accurate control data for comparison since the control group will have been participating in the Being a Parent program. Concurrently, a qualitative process assessment will be performed using semi-structured interviews to thoroughly explore the experience of the families who participated in the Being a Parent program, independently of their designated trial group. Figure 1 summarizes the participant flow throughout the study. As illustrated, parents will be recruited through different channels and will be asked to sign in through our website. If included in the study, participants will complete baseline assessments and proceed to randomization to either an intervention group or a control group. Post-intervention assessments will be completed by both groups, and the intervention group will have an additional 6-month assessment. Qualitative assessments will also be conducted.

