### 2.6. Measures

#### 2.6.1. Feasibility, Fidelity, and Acceptability

Structured sheets will be used to record significant feasibility parameters associated with trial methodology and program implementation. This will enable the assessment of participants’ rates related to (a) enrolment; (b) eligibility; (c) intervention attendance and retention; and (d) data collection. Dropout will also be recorded for both arms, as well as missed sessions for the experimental group. The research team, with the help of the group leaders, will fill out weekly review forms to assess fidelity criteria (e.g., the delivery of content; alignment with intervention methods and strategies). In addition, a treatment acceptability rating scale (TARS) created by the Empowering Parents, Empowering Communities team will be completed by the participants from the experimental group post-intervention. This scale was specifically created in order to assess the unique aspects of treatment acceptability that are specific to the Being a Parent program. It comprises 12 tailored items in which parents will report on satisfaction with intervention delivery. Questions reflect the content and delivery style of this specific parenting program, ensuring that the assessment is both contextually relevant and comprehensive (e.g., “*In general, are you satisfied with group leaders?*”).

A qualitative semi-structured interview will also be conducted post-intervention with a small sample of the participants from the experimental group. The main goal is to better understand the experiences of parents that participate in the parenting program. Therefore, topic guides will include open prompts regarding (a) trial implementation (e.g., recruitment and data collection); (b) intervention implementation (e.g., localization and dates); (c) intervention acceptability (e.g., content and impact); and (d) the adequacy of group leaders (e.g., competencies).

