### 2.7. Sample Size

Sample size calculation was based on the CONSORT 2010 statement extended to feasibility trials [35] and the Lewis et al. [36] methodology. This approach calculates sample size by conducting hypothesis testing based on estimations of predefined feasibility outcomes being within the unacceptable “red zone” (null hypothesis) and contrasting this with an alternative hypothesis of being within the “favorable” green zone [35]. A sample size is considered appropriate if it allows for ≥80% power to reject being in the red zone if the green zone holds true. For detailed information about this methodology, please consult Lewis et al. [36].

Progression parameters and their subsequent point estimates as described in Table 2 were used. Considering a one-tailed, one-sample binomial test based on normal approximation (with continuity correction) with α = 0.05, the following minimum sample sizes for each parameter were obtained:Feasibility of participant retention at post-intervention (Rul = 0.50 and Gll = 0.70)—41 participantsFeasibility of consent rate (Rul = 0.40 and Gll = 0.60)—42 participantsFeasibility of program completion (Rul = 0.45 and Gll = 0.75)—18 participants (intervention arm)Feasibility of program acceptability (Rul = 0.45 and Gll = 0.75)—19 participants (intervention arm)Feasibility of program fidelity (Rul = 0.40 and Gll = 0.70)—19 participants (intervention arm)

Therefore, a sample size of 42 participants, with 25 participants in the intervention arm, allows for ≥80% power to reject the null hypothesis for each of the feasibility outcomes. Moreover, this sample size is sufficient for the estimation of effect sizes for a future larger trial, as it allows for the collection of preliminary data needed to calculate reliable effect size estimates and assess the variability in psychological measures.

Regarding our qualitative data, according to the recommendations of Boddy [37] and van Risjnsoever [38], we aim to recruit 10 to 12 participants, as this sample size is often sufficient to achieve data saturation when the aim is to explore shared experiences within a relatively homogeneous group. Moreover, we will closely monitor data saturation during analysis and will adjust the sample size if necessary to ensure robust and meaningful findings.

**Table 2 healthcare-13-00176-t002:** Feasibility progression parameters.

Parameter	Thresholds		Justification

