4. Feasibility of Program Acceptability *Does an appropriate number of families from the intervention arm rate the BaP program acceptable?*	GREEN ZONE (Go—Proceed with full RCT)	>75%	Program acceptability is an important criterion in considering if the BaP program will be well received in the Portuguese community Program acceptability will be measured using the treatment acceptability rating scale (TARS) A total score of 27 or more equates to ratings of “Quite a lot” or “A great deal” on each item Previous trials of the BaP program found that an average of 98.5% of participants had total scores ≥ 27 [19] A conservative threshold of 75% will be used
	AMBER ZONE (Amend—Proceed with changes)	45–75%	
	RED ZONE (Stop—Do not proceed unless significant changes are made)	<45%	
5. Feasibility of Program Fidelity *Can the BaP intervention be delivered as planned?*	GREEN ZONE (Go—Proceed with full RCT)	>70%	For the BaP program, 75% fidelity is considered appropriate, which would mean that six out of eight sessions were delivered as planned Fidelity estimates serve as indicators to identify deviations from the designed intervention delivery, exposing potential issues like methodological challenges and variances with local contexts [44] Increasing fidelity correlates with improved outcomes [44] Conservative estimates of fidelity rates are used because this is the first time the BaP program will be tested in a Portuguese context, and thus, cultural and linguistic factors can significantly impact fidelity
	AMBER ZONE (Amend—Proceed with changes)	40–70%	
	RED ZONE (Stop—Do not proceed unless significant changes are made)	<40%	

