### 2.8. Data Analysis Strategy

#### 2.8.1. Quantitative Data

Quantitative data will be analyzed using IBM SPSS Statistics (version 28). The analysis and presentation of data will be in accordance with CONSORT guidelines, in particular the extension to feasibility and pilot trials [35].

Descriptive statistics will be computed to assess feasibility and acceptability. Fidelity data collected from the weekly review forms will be assessed based on a cumulative score across sessions, as well as a percentage of the maximum cumulative score. Standard descriptive statistics will be computed to report demographics, as well as baseline and outcome scores. An intention-to-treat (ITT) analysis approach will be employed to ensure the validity and generalizability of study findings by minimizing bias and providing a robust assessment of treatment effects [45]. Effectiveness analyses, using data from our psychological measures, will be performed with data from Parent 1, while data collected from Parent 2 will be examined independently to consolidate our findings. An analysis of covariance (ANCOVA) will be used to examine differences between intervention and waitlist control arms, taking pre-intervention data into account as a covariate. Cohen’s d effect sizes will be calculated, as well as 95% confidence intervals. Data from Parent 1 and Parent 2 will be compared using paired-samples sign tests in order to determine if there were any differences in the median values of their observations.

When the assumption of homogeneity of regression is not met, transformations will be performed on pre-intervention data. Moreover, Little’s test [46] will be conducted to examine the underlying nature of our missing data. If missing data are missing completely at random (MCAR), a Last Observation Carried Forward (LOCF) framework will be used.

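### Fidelity is sized and powered in participants although it is measured on delivered sessions, so its 80% power claim has no valid basis as written, and Table 2 does not say which fidelity percentage its limits govern

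*Protocol article*

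**What the plan says.** Section 2.7 sizes all five progression parameters with one method: "Considering a one-tailed, one-sample binomial test based on normal approximation (with continuity correction) with α = 0.05", requiring "≥80% power to reject being in the red zone if the green zone holds true". For fidelity it gives "Feasibility of program fidelity (Rul = 0.40 and Gll = 0.70)—19 participants (intervention arm"). It then concludes that 42 participants, "with 25 participants in the intervention arm", meet the power requirement for each feasibility outcome.

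Three other places describe what fidelity is:

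- Section 2.6.1: the research team, helped by the group leaders, "will fill out weekly review forms to assess fidelity criteria". The examples given are content delivery and alignment with the intervention's methods.
- Table 2, row 5: the question is whether the intervention can be delivered as planned. The justification column says that 75% is considered appropriate, "which would mean that six out of eight sessions were delivered as planned". The zones are green above 70%, amber 40–70% and red below 40%.
- Section 2.8.1: fidelity is a cumulative score across sessions, "as well as a percentage of the maximum cumulative score".

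**The concern.** A one-sample binomial test on 19 participants needs 19 yes/no observations, one per participant. The article defines no such observation for fidelity. The forms describe what the leaders delivered, and everyone in a group receives the same delivery. Recruiting another parent adds fidelity data only if it leads to another group. The number of binomial trials is therefore set by the number of groups times eight sessions, not by the size of the arm.

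There is a second, smaller point. The share of sessions delivered as planned is a binomial proportion; a percentage of a maximum score in general is not. Table 2 does not say which of the two is held against its limits.

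Fidelity is one of five criteria for proceeding to a full trial, and its red zone means stop. Its power statement should refer to data that will exist, and its metric should be fixed before the forms are read.

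**Working it through.** **1. Reproducing the plan's figure.** Inputs from section 2.7: p0 = 0.40, p1 = 0.70, one-sided α = 0.05 (z = 1.645), power 80% (z = 0.842).

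- Without correction: n = [(1.645·√(0.40·0.60) + 0.842·√(0.70·0.30)) / 0.30]² = 15.77.
- With continuity correction: (n/4)·[1 + √(1 + 2/(n·0.30))]² = 18.96, rounded up to 19.
- Exact check at n = 19: reject at 12 or more, actual α 0.035, power 0.818.

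The figure 19 is correct as a number of independent binomial trials.

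**2. How many groups.** The article does not say. Section 2.4 describes groups of 7 to 12 parents for the original program and a minimum of five to start a group in this trial. I take 12 as the upper limit here too, which is an assumption.

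- Arm of 25: 25/12 = 2.08, so at least three groups; at five per group, at most five.
- Arm of 21, which is what 42 participants give "with a 1:1 allocation ratio" (section 2.1): 21/12 = 1.75, so at least two groups; at five per group, at most four.
- Two groups hold at most 24 parents, so two groups are possible only if the arm is about 21–24 parents.

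**3. Power with sessions as the unit.** Sessions = 8 × groups, one fidelity result per session per group (inferred from the weekly forms), sessions independent. Exact power is the binomial tail at p = 0.70. The approximation is Φ{[n·p1 − (n·p0 + 0.5 + 1.645·√(n·p0(1−p0)))] / √(n·p1(1−p1))}.

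| Groups | Sessions | Reject at | Exact power | Approximation |
|---|---|---|---|---|
| 2 | 16 | ≥11 | 66% | 72% |
| 3 | 24 | ≥15 | 85% | 89% |
| 4 | 32 | ≥18 | 97% | 96% |
| 5 | 40 | ≥22 | 99% | 99% |

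**4. Correlated sessions.** Section 2.4 has the same two psychologists lead all groups. The article gives no intraclass correlation (ICC), so I assume 0.05 to 0.30 within a group, with design effect 1 + 7·ICC. For three groups at ICC 0.05 the effective number is 24/1.35 = 17.8. Power by the approximation:

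| Groups | ICC 0.05 | ICC 0.10 | ICC 0.30 |
|---|---|---|---|
| 2 | 57% | 46% | 23% |
| 3 | 77% | 66% | 37% |
| 4 | 89% | 80% | 50% |
| 5 | 95% | 88% | 61% |

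Correlation across groups through the shared leaders is not captured here and would reduce power further.

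**5. The two percentages.** If each session is scored simply as delivered or not, they coincide: 6/8 = 75% on both. If the forms give part marks, they can differ. Take one course with equal maximum marks per session, five sessions fully delivered and three partly delivered and not counted as planned. The share is 5/8 = 62.5%, which is amber. The score passes 70% once the three partial sessions together earn more than 0.70·8 − 5 = 0.6 of one session's marks, which is green.

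**The case against.** Much of the opposing case stands.

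- **No deficit is shown.** A reader might infer that fidelity is underpowered. At the stated arm of 25 and at most 12 per group there are at least three groups, and 24 independent sessions give 85%. The 66% figure needs an arm of about 21–24 parents in two groups. Groups are counted in parents and both parents may attend, so 21 families with four second parents already make 25 people and need a third group.
- **The test serves sizing only.** Section 2.8.1 analyzes feasibility descriptively and Table 2 decides by zone. Consent (42) and retention (41) drive the total, so correcting the unit changes neither the sample size nor the limits.
- **The metrics need not conflict.** A reader might call them incompatible, or picture every session scoring in the green range while none counts as planned. That picture needs a definition of as planned that the article does not give. The six-of-eight remark is a justification note, and the form's scoring may well be set out in a fuller document.

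What does not stand is the reply that all of this may be left to a fuller document. The article itself fixes the test, the unit, the 19 and the power claim, and the unit disagrees with its own description of how fidelity is measured.

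**Conclusion.** The point holds in limited form. The number 19 is computed correctly but attached to participants, who are not the unit of fidelity. The claim of at least 80% power for this one of five progression parameters therefore has no valid basis as written.

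On sessions, exact power runs from about 66% (two groups) through 85% (three) to 97% (four) if sessions are independent, and it is lower under correlation. With three groups, an ICC as small as 0.05 brings it to about 77%. A value below 80% is possible but not established. It depends on the number of groups, which is not stated, and on a correlation that I have assumed.

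The zone limits are clear, but the percentage they apply to is not named. This should be fixed. It does not threaten the trial's design or its total size.

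**What to change.** In section 2.7, do one of two things:

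- remove fidelity from the participant-based power statement and report it descriptively; or
- restate the requirement in sessions, give the planned number of groups and hence sessions, and call the power nominal because sessions share leaders.

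In Table 2, name the single percentage that is compared with the 40% and 70% limits: the share of sessions delivered as planned, or the percentage of the maximum cumulative score. Report the other descriptively. If the share is chosen, say what makes a session count as delivered as planned, or refer to the form if it already defines this.

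The cost is wording. The weekly forms are already planned, and the total sample size and the limits stay as they are. The small downside is that the power stated for fidelity becomes nominal or is dropped.

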### 2.2. Participants and Eligibility

The participants will be primary caregivers from the district of Lisbon or Setúbal (Portugal) with a child between the ages of 2 and 11 years old. One or both parents can choose to participate. Families will be eligible for inclusion if a parent identifies difficulties in managing the child’s behavior. Since the Being a Parent program is designed to improve parenting skills for the management of behavioral issues, as long as parents are struggling with child behavior, they are likely to find the intervention helpful. As exclusion criteria, the following principles were defined: (a) families where the index child is in foster care or in an adoption process at the time of the study, as such children are not cohabiting with their parents; (b) parents of children with severe neurodevelopmental problems (such as autism), as children with neurodevelopmental disabilities often require specialized interventions; and (c) parents who are engaged in another structured parenting intervention; and (d) parents who are unable to read or write Portuguese.

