#### 2.3.2. Randomization

The randomization of participants will occur after the collection of baseline data and will be conducted only by one researcher, assuring that the rest of the research team will be blinded to randomization. Participants will be randomly assigned to either the intervention group or the waitlist control group using block randomization to ensure balanced allocation across key variables that could influence the study outcomes. Blocks will be created using Random Allocation Software (version 2.0) and will be based on four stratification variables: child’s age (categorized into predefined age ranges to account for developmental differences), child’s sex (male or female, as behavioral outcomes may vary by gender), socioeconomic status (SES; classified into low, medium, or high, based on parental education), and whether one or both parents of a family unit will participate. Within each block, participants will be randomly assigned to groups using a computer-generated randomization sequence, ensuring equal distribution across intervention and control groups. This approach will minimize confounds by balancing critical baseline characteristics and will enhance the internal validity of the study [25]. Additionally, to ensure transparency and replicability, the randomization sequence and its implementation will be documented in detail and securely stored for auditing purposes.

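### The sample-size statement puts 25 of 42 in the intervention arm, but 1:1 allocation gives 21; the acceptability test then reaches 80% power only with near-complete return of the acceptability scale

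*Protocol article*

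**What the plan says.** Section 2.7 sizes the trial on five progression parameters. Its method is: "Considering a one-tailed, one-sample binomial test based on normal approximation (with continuity correction) with α = 0.05". Its criterion is: "A sample size is considered appropriate if it allows for ≥80% power to reject being in the red zone if the green zone holds true". The minimum numbers are 41 for retention and 42 for consent. In the intervention arm alone they are 18 for completion, 19 for acceptability and 19 for fidelity. The conclusion is: "Therefore, a sample size of 42 participants, with 25 participants in the intervention arm, allows for ≥80% power to reject the null hypothesis" for each outcome.

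Section 2.1 states that "families will be randomly assigned to an intervention arm and a waitlist control arm, with a 1:1 allocation ratio". Section 2.3.2 describes the randomisation as "ensuring equal distribution across intervention and control groups".

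Acceptability is measured with the TARS, which according to section 2.6.1 "will be completed by the participants from the experimental group post-intervention". Section 2.7 states no allowance for missing forms. Table 2 cites 80% average retention in earlier trials of this program and 9 to 27% attrition in comparable trials, and sets the green limit for retention at 70%.

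On the unit, section 2.7 counts participants. Section 2.1 randomises families, Table 2 frames retention, consent and acceptability on families, and section 2.2 says: "One or both parents can choose to participate".

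**The concern.** The sentence that justifies the sample size describes a split that the randomisation is not designed to produce. Twenty-five of 42 leaves 17 controls, a ratio of about 1.47:1, and no reason for unequal arms is given. One of three figures must change: the total, the arm size or the ratio.

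This matters because three of the five go/amend/stop parameters are assessed in the intervention arm only. The four extra participants implied by 25 instead of 21 make up most of the margin above the required 19. Acceptability is the most exposed, because its data come from a form completed after the intervention, when some families will have been lost.

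**Working it through.** **Inputs.** Acceptability: p0 = 0.45, p1 = 0.75, one-sided α = 0.05 (z = 1.645), target power 80% (z = 0.842), all from section 2.7. Allocation is 1:1 (section 2.1). Retention figures come from Table 2.

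**1. The plan's own figure.**
n0 = [1.645·√(0.45·0.55) + 0.842·√(0.75·0.25)]² / 0.30² = (0.818 + 0.364)² / 0.09 = 15.54.
With continuity correction: n = (n0/4)·[1 + √(1 + 2/(n0·0.30))]² = 18.73, so 19. This matches the plan. Fidelity (0.40 against 0.70) gives 18.96, so 19, which also matches.

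**2. Arm size.** 42/2 = 21 per arm. 25 × 2 = 50. 42 − 25 = 17.

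**3. Power at 21 with complete data.**
Power = Φ{[√n·(p1 − p0 − 1/(2n)) − 1.645·√(p0·q0)] / √(p1·q1)}.
Acceptability: (1.266 − 0.818)/0.433 = 1.033, so 84.9%.

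| Test at n = 21 | Continuity-corrected | Exact binomial |
|---|---|---|
| Acceptability, 0.45 v 0.75 | 84.9% | 87.0% (reject at 14 or more of 21) |
| Fidelity, 0.40 v 0.70 | 84.2% | 85.2% |
| Completion, 0.45 v 0.75 (section 2.7) | 84.9% | 87.0% |
| Completion, 0.30 v 0.60 (Table 2) | 85.2% | 82.6% |

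All exceed 80%. The completion rates differ between section 2.7 and Table 2, but either pair passes at 21.

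**4. Acceptability when forms are missing.** The number of forms returned is taken as Binomial(N, r), and power is averaged over it. The return rate r is an assumption; 80% is the retention cited for this program, 73% and 91% correspond to the cited 27% and 9% attrition, and 70% is the green limit for retention.

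| Return r | N = 21: corrected / exact | Chance of at least 19 forms, N = 21 |
|---|---|---|
| 70% | 67.2% / 70.1% | 3% |
| 73% | 69.5% / 72.1% | 5% |
| 80% | 74.3% / 75.5% | 18% |
| 91% | 80.7% / 79.5% | 71% |

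With N = 25 and 80% return, power is 82.4% / 81.6%, and the chance of at least 19 forms is 78%.

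Averaging is needed because exact power does not rise smoothly with n: it is 81.0% at 16 forms, 76.5% at 17 and 71.7% at 18.

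**The case against.** The strongest reply is that the arm-size contradiction costs nothing by itself. A reader might infer that 21 per arm breaks the 80% claim. It does not: the plan's own minima of 18, 19 and 19 are all below 21, and step 3 of the working confirms it. That reply stands, so the shortfall is a matter of missing forms and rests on an assumed return rate. The plan gives no TARS return rate; overall retention is only a stand-in. The 70% figure is a progression threshold, not an expected rate.

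A second reply is that true acceptability may be far above 75%. Table 2 cites 98.5% in earlier work and calls 75% conservative. At 98.5% the test would have ample power even with few forms, so the practical risk to this go/stop decision may be small. But section 2.7 defines adequacy at the edge of the green zone, and its claim has to be judged there.

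A reader might also infer that retention is underpowered, because 42 participants could mean caregivers from fewer than 42 families. The documents do not support that. Table 2 defines retention and consent on families, section 2.1 randomises families, and no two-parent rate is given from which a shortfall could be computed. What remains is loose wording in section 2.7.

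**Conclusion.** The contradiction is certain from the text: 25 of 42 cannot be reconciled with 1:1 allocation. With complete data at 21 per arm, the three intervention-arm tests keep at least 80% power.

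For acceptability the claim has little slack. An arm of 21 can lose two forms before falling under the plan's minimum of 19. If TARS return equals the cited 80% retention, the difference between 21 and 25 decides whether the claim is met: about 74–76% against about 82%. Over the attrition range in Table 2, power with 21 runs from about 70–72% (73% return) to a borderline 79–81% (91% return). These figures assume true acceptability of exactly 75% and independent return of forms at a common rate.

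**What to change.** - Reconcile section 2.7 with sections 2.1 and 2.3.2. Without further enrolment, write 42 randomised families, 21 per arm, counted by family as in Table 2. Keeping 25 per arm at 1:1 would instead mean 50 families, eight more.
- If 42 is kept, replace the blanket power statement for acceptability: about 85% with all forms returned and about 74–76% at 80% return, so that at least 80% holds only with near-complete return.
- State that the TARS is sought from every intervention-arm family, including those who stopped attending.

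The cost at 42 families is a few sentences, a less favourable power figure for one parameter, and reminders for a 12-item form. No design change or additional enrolment is needed.

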### 2.4. The Portuguese Being a Parent Program

The Being a Parent intervention is part of the Empowering Parents, Empowering Communities program developed in the United Kingdom (UK) by the Centre for Parent and Child Support at South London and Maudsley NHS Foundation Trust (SLAM) and the Child and Adolescent Mental Health Services (CAMHS) Research Unit at King’s College London. It consists of eight weekly sessions plus an optional introductory session, each with a duration of two hours, facilitated by two accredited parents of the community and directed at groups of seven to twelve parents [18].

Built on attachment theory, family systems theory and cognitive–behavioral frameworks, it is rooted in empirically validated parenting strategies that specifically address the most common issues present in children aged two to eleven years old with behavioral problems [19]. Each session is characterized by its high degree of interactivity, featuring a dynamic combination of small and large group discussions, role-playing, demonstrations, the sharing of experiences, and reflective exercises [19]. Table 1 describes in detail the content discussed in each session.

Adapting the Being a Parent intervention to the Portuguese community encompassed pertinent cultural and delivery changes. Following a stacked intervention adaptation model, namely, the Ecological Validity Model (EVM) [23,26] and the Cultural Adaptation Process (CAP) [27], the Being a Parent program was translated to Portuguese, and minor changes related to linguistic features were implemented in order to culturally adapt the intervention. No content modifications were made due to the fact that all topics and exercises were considered pertinent to the Portuguese context, despite cultural differences that may exist. Due to legal aspects, the main modification in the Portuguese version was focused on program delivery. Instead of using a peer-led approach, the Portuguese version will be professionally led, meaning that two accredited psychologists with experience in child and familial problems will deliver the intervention.

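### Section 2.7 says 42 participants suffice for reliable effect sizes, but the 42 rests only on feasibility rates, and the expected 95% interval is about ±0.4 to ±0.75 SD

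*Protocol article*

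**What the plan says.** Section 2.7 of the Protocol article sizes the trial on five feasibility proportions: "Considering a one-tailed, one-sample binomial test based on normal approximation (with continuity correction) with α = 0.05". It settles on "a sample size of 42 participants, with 25 participants in the intervention arm" and claims at least 80% power for each of the five parameters. It then extends the claim to the psychological outcomes: "this sample size is sufficient for the estimation of effect sizes for a future larger trial". The only ground offered for this extension is what the data would permit, namely that 42 is adequate "as it allows for the collection of preliminary data needed to calculate reliable effect size estimates and assess the variability in psychological measures". No SD, correlation, target effect or target interval width accompanies this statement.

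Section 2.8.1 fixes the effectiveness analysis: "An analysis of covariance (ANCOVA) will be used to examine differences between intervention and waitlist control arms". The pre-intervention score is the covariate, Parent 1 supplies the data, and Cohen's d and 95% confidence intervals are reported. No group term is named.

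Section 2.4 describes group delivery. The original program is "directed at groups of seven to twelve parents", and the Portuguese version needs at least five members to start a group. Under 2.1 and 2.5 the waitlist arm receives nothing before the post-intervention assessment, so it has no groups at that point.

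**The concern.** A sample size that can tell a 40% consent rate from a 60% one says nothing about how well a between-arm mean difference is estimated. Section 2.7 nevertheless moves from the first to the second and names the future trial as the use of the effect sizes. A planner who took the word *reliable* at face value could size the full RCT on a d whose interval runs from almost nothing to very large.

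A second issue bears on the same interval. Only the intervention arm is treated in groups. If families in one group end up more alike than families in different groups, an ANCOVA that treats all families as independent understates the standard error, and the printed interval hides part of the imprecision.

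**Working it through.** **Inputs from the article.** One-sided α of 0.05 and 80% power for each feasibility parameter (2.7). Total of 42, read as 21/21 from "with a 1:1 allocation ratio" (2.1) or as 25/17 from the 25 intervention participants in 2.7; both are carried below. Retention: 80% on average in earlier trials of the program, and 70% as the edge of the green zone (Table 2).

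**Assumptions, because the article gives no figure.** Baseline-post correlation ρ from 0 to 0.8. Residual within-group ICC from 0.05 to 0.15. Two or three intervention groups (25/12 ≈ 2.1 and 21/7 = 3 at the stated group sizes).

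**1. The plan's own figure.** Take n = [(1.645√(p0q0) + 0.842√(p1q1))/δ]², with δ = p1 − p0, then the continuity correction n/4 × (1 + √(1 + 2/(nδ)))².

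- 0.50 vs 0.70: 41.3 (stated 41)
- 0.40 vs 0.60: 41.9 (stated 42)
- 0.45 vs 0.75: 18.7 (stated 18 and 19)
- 0.40 vs 0.70: 19.0 (stated 19)

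The maximum of 42 reproduces. It depends only on proportions.

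**2. Precision of the standardised difference.** Half-width = t(0.975, df) × √[(1 − ρ²)(1/n₁ + 1/n₂)], in SD units. Example, 21/21 with ρ = 0.7: 2.023 × √(0.51 × 2/21) = 0.45.

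| Data | ρ = 0 | 0.5 | 0.7 | 0.8 |
|---|---|---|---|---|
| 21/21, complete | 0.62 | 0.54 | 0.45 | 0.37 |
| 25/17, complete | 0.64 | 0.55 | 0.45 | 0.38 |
| 21/21, 80% retained | 0.70 | 0.61 | 0.50 | 0.42 |
| 25/17, 80% retained | 0.72 | 0.62 | 0.51 | 0.43 |
| 15/14 (21/21 at 70%) | 0.76 | 0.66 | 0.55 | 0.46 |

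A cross-check with the unadjusted formula SE(d) = √(1/n₁ + 1/n₂ + d²/(2(n₁ + n₂))) at d = 0.5:

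- 21/21: SE 0.313, interval −0.11 to 1.11
- 15/14: SE 0.377, interval −0.24 to 1.24

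**3. What this means for sizing.** At 80% retention the half-width is 0.5 or more unless ρ exceeds about 0.7, so an observed 0.5 does not clear zero. Take the more favourable 0.42 (21/21, 80% retained, ρ = 0.8): 0.5 ± 0.42 runs from 0.08 to 0.92. With n per arm = 2((1.96 + 0.84)/d)² at 80% power and two-sided 5%, the next trial would need 2453, 63 or 19 per arm at the lower limit, the estimate and the upper limit. The SD is also uncertain: its 95% interval is about 0.82 to 1.28 times the estimate on 40 df.

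**4. Effect of the groups, if the ICC is above zero.** With DE = 1 + (m − 1)ICC in the intervention arm only, the 21/21 standard error grows by √((DE + 1)/2). For m = 7 and ICC 0.05, 0.10, 0.15, DE is 1.30, 1.60, 1.90 and the factor is 1.07, 1.14, 1.20. Simulated coverage of the plain ANCOVA 95% interval (ρ = 0.7):

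| Groups | ICC 0.05 | 0.10 | 0.15 |
|---|---|---|---|
| Three of seven | 93% | 91% | 89–90% |
| Two of ten | 92% | 89% | 87% |

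At ICC 0, coverage is 95%.

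**5. Can the group variance be estimated?** The chance that a balanced one-way ANOVA puts it at or below zero is P(F ≤ 1/(1 + m·ICC/(1 − ICC))) on k − 1 and k(m − 1) df, for k groups of m. With three groups of seven this is 50%, 42% and 35% at the three ICCs. With two groups of ten it is 57%, 50% and about 45%.

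**The case against.** Effectiveness is framed as exploratory in the abstract and the aims. No progression criterion in Table 2 uses an effect size, and 2.8.1 commits to reporting 95% intervals, so readers will see most of the imprecision. This stands and limits the harm, but it does not make the claim in 2.7 true.

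A reader might infer that the full RCT will be sized on the observed d. The article does not say so. Section 2.7 also mentions the variability of the measures, and Table 2 says retention will inform the later sample size. The mis-sizing is a risk that the wording invites, not a stated plan.

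A reader might also infer that the ANCOVA is bound to print intervals that are too narrow. That does not follow. It needs a residual ICC above zero, and no ICC is given. The number of groups is inferred, the range of seven to twelve describes parents in the original program, and two parents of one family may attend while only Parent 1 is analysed, so there may be fewer analysed families per group. The same two psychologists lead every group, which removes much of one source of between-group variance. At an ICC of 0.05 with three groups the loss is about two percentage points of coverage.

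Finally, a partially nested model would often estimate the group variance as zero and return the plain ANCOVA. This stands, and it argues for a sensitivity analysis as the main remedy. Leaving a group term to an analysis plan that is not shown would also be defensible; the point about 2.7 does not depend on it.

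**Conclusion.** The claim in 2.7 is unsupported and should be changed. A plausible middle case (80% retained, ρ 0.5 to 0.7) gives ±0.5 to ±0.6 SD. The ends of the range, about ±0.37 and ±0.76, need respectively complete data with ρ = 0.8, and 70% retention with no baseline adjustment. The Discussion expects moderate to large effects, and a moderate one would often not be separated from zero. This holds for either reading of the allocation and needs no assumption about clustering.

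The clustering point is conditional: the direction is clear if the ICC is positive, and its size (coverage of about 93% to 87%) rests on the assumed ICC of 0.05 to 0.15 and on two or three groups.

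Two further features could add to the imprecision or hide it. Last-observation-carried-forward could keep the nominal n at 42 despite dropout. If the 42 counts parents rather than families, the Parent 1 analysis has fewer than 42.

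**What to change.** In 2.7, remove the words *sufficient* and *reliable* as applied to effect sizes. State the expected 95% half-width with its assumptions, for example about 0.5 to 0.6 SD at 80% retention and correlation 0.5 to 0.7. Say that d with its interval is exploratory, and that the full RCT will not be sized on the observed d alone but on a minimum important difference, with the observed SD (allowing for its uncertainty) and retention.

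In 2.8.1, keep the ANCOVA. Add a sensitivity interval that multiplies the intervention-arm variance by 1 + (m − 1)ICC over a stated range such as 0.05 to 0.15. A partially nested mixed model can be shown as an option, with the caveat that two to four groups estimate the group variance poorly.

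The cost is wording and one short extra calculation, with no change to recruitment or data collection. The downside is a less favourable stated precision and a slightly wider sensitivity interval.
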